## Abstract

**Background:**

The spine is the most frequent location of bone metastases. Local treatment aims at palliation of pain and, given the increased likelihood of long-term cancer survival, at local control. Kyphoplasty and intraoperative radiotherapy (Kypho-IORT) provided instantaneous pain relief in 70% of patients at the first day after the intervention and resulted in local control rates of > 93% at 1 year in a recently conducted phase I/II trial. To assess its clinical value, we designed a phase III trial which tests Kypho-IORT against the most widespread standard-of-care, external beam radiotherapy (EBRT), in patients with painful vertebral metastases.

**Methods:**

This phase III study includes patients ≥50 years of age with up to 4 vertebral metastases and a pain score of at least 3/10 points on the visual/numeric analogy scale (VAS). Patients randomized into the experimental arm (A) will undergo Kypho-IORT (Kyphoplasty plus IORT with 8 Gy prescribed to 13 mm depth). Patients randomized into the control arm (B) will receive EBRT with either 30 Gy in 10 fractions or 8 Gy as a single dose. The primary end point is pain reduction defined as at least − 3 points on the VAS compared to baseline at day 1. Assuming that 40% of patients in the Kypho-IORT arm and 5% of patients in the control arm will achieve this reduction and 20% will drop out, a total of 54 patients will have to be included to reach a power of 0.817 with a two-sided alpha of 0.05. Secondary endpoints are evaluation of the percentage of patients with a pain reduction of at least 3 points at 2 and 6 weeks, local tumor control, frequency of re-intervention, secondary fractures/sintering, complication rates, skin toxicity/wound healing, progression-free survival (PFS), overall survival (OS) and quality of life.

**Discussion:**

This trial will generate level 1 evidence on the clinical value of a one-stop procedure which may provide instantaneous pain relief, long-term control and shortened intervals to further adjuvant (systemic) therapies in patients with spinal metastases.

**Trial registration:**

Registered with ClinicalTrials.gov, number: NCT02773966 (Registration date: 05/16/2016).

## Background

Due to optimized therapies, life expectancy of patients with metastasizing cancer will continue to rise. Bone metastases affect 10–30% of all cancer patients, especially those located in the vertebral column. The main clinical problems are severe back pain and an increased risk of pathological fractures. Therefore, optimized palliative treatments to improve quality of life are necessary.

External beam radiotherapy (EBRT) is a well-established treatment option for patients with spinal metastases. EBRT results in adequate pain relief with acceptable local tumor control [1]. Of the retrospective series that described pain outcome mentioned in the systematic review by Gerszten et al., roughly 70% of patients had improvement in pain after radiation therapy [1]. The mean rate of local control was 77% (range, 61–89%). Although EBRT is the standard treatment for painful vertebral metastases, neither the optimal fractionation schedule nor the optimal standard dose have been established yet [2].

The two most common schemes are either 10 fractions of 3 Gy (30 Gy total dose) or a single-shot irradiation with 8 Gy [3]. Although EBRT is tolerated well and local control rates are acceptable, pain relief occurs delayed (within weeks) after EBRT, which in the light of the short life expectancy is unsatisfactory [4]. Based on data from the Bone Pain Trial [5], one can assume that as few as 20% of patients will experience pain relief within the first weeks.

Balloon kyphoplasty is a valuable treatment option for patients with painful and instable metastases to the vertebral column. In the CAFE trial [6], 134 patients with vertebral compression fractures were enrolled and randomly assigned to kyphoplasty or non-surgical management. The study found that patients treated with kyphoplasty had a significant reduction of back pain (from a numeric rating score [NRS] of 7.0 at baseline to 3.5 after kyphoplasty) after seven days.

However, kyphoplasty alone has no documented anticancer effect and thus EBRT is required to avoid early tumor regrowth. As this may take another 2–4 weeks (due to reduction of single doses to account for wound healing, e.g. 30Gy in 15 or 40 Gy in 20 fractions), this prolonged treatment poses an unacceptable mental and physical challenge to patients. These considerations also apply for 1times 8Gy, albeit not that distinct. Moreover, patients with progressive or simultaneous (e.g. visceral) metastases may also urgently require chemotherapy, which cannot be applied concurrently to radiotherapy due to the risk of potentiated toxicity.

To reduce treatment time and at the same time increase quality of life, novel techniques like kyphoplasty combined with (physical) anticancer methods are required. Our group developed a novel approach to deliver intraoperative radiotherapy during kyphoplasty (Kypho-IORT) [7–10]. In a recent dose escalation and cohort expansion phase I/II trial we enrolled 61 patients aged 50 years and older with a Karnofsky Performance Status of at least 60% and with one to three painful vertebral metastases confined to the vertebral body [11]. We detected that, after Kypho-IORT, the median pain score significantly dropped from 5 preoperatively to 2 at the first postoperative day (*p* < .001) and a persistent pain reduction beyond the first postoperative day of ≥3 points in 34 (79.1%) patients. As the 3, 6, and 12 month local progression-free-survival (L-PFS) was excellent with 97.5, 93.8, and 93.8%, we set up this randomized phase III trial to investigate whether this new technology may have the potential to replace the current standard of care.

## Methods/design

### Study design

This protocol (Version 2.0, April 2016) describes a prospective, multicenter, randomized phase III study set up to assess pain reduction after Kypho-IORT (Arm A) or EBRT (Arm B) for spinal metastases (Fig. 1). Patients will be recruited over a period of 2.5 years and followed to a maximum of 5 years.

**Fig. 1 Fig1:**
[figure not shown]
Trial Workflow. *study centers may choose between fractionated EBRT (30 Gy in 10 fractions) or single-dose EBRT (1 × 8 Gy). Once an option is chosen, the center must adhere to it for all patients included into the trial. Legend: IORT- intraoperative radiotherapy; Kypho-IORT – kyphoplasty or vertebroplasty + IORT; EBRT – external beam radiotherapy

### Objective and primary endpoint

The primary objective of this study is to test if the analgesic efficiency of Kypho-IORT is superior to standard-of-care EBRT in patients with painful vertebral metastases. The primary end point is to evaluate the percentages of patients with a pain reduction of at least 3 points (VAS) at the first post-interventional day (i.e. one day after Kypho-IORT in Arm A and one day after the begin of fractionated or single-shot EBRT in Arm B).

### Secondary endpoints

Secondary objectives arepercentage of patients with a pain reduction of at least 3 points on VAS at week 2 and 6 weeks after start of treatmentlocal tumor control, measured by longitudinal CT/MRI scans done at FUs by assigning one of the following lesion states: stable, osteoradionecrosis, pathological fracture, sintering progression, local relapsefrequency of re-intervention or salvage therapies to the treated sitesecondary fractures/sintering progressionoverall progression-free survivaladverse eventsincidence of cement leakage (including direction of leakage; symptomatic vs. asymptomatic)skin toxicity/wound healing, documented by regular imaging of the scarquality of life, assessed by completion of EORTC QLQ C30 and BM22 questionnaires

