#### Local tumor control, progression-free survival

At each follow-up visit (after 6 weeks, 3 months and thereafter each 6 months), there will be either a MRI or CT scan of the (complete) spine to determine the response of the treated lesion (stable, osteoradionecrosis, pathological fracture, sintering progression, local relapse) and to monitor for new metastases to other regions of the spine (we recommend the same diagnostic routine, which led to the treatment). Local control is defined as time span between randomization and local progression. Local progression is assessed either by serial CT or MRI scanning. Indicators for local progression in CT scans are:increase in size of osteolytic areasdevelopment of epidural diseaseprogressive sintering/fracture of the treated vertebral body

Once progression is suspected in CT scans, a contrast-enhanced MRI should be performed, whereas indicators of progression areincrease in the T2-signalepidural disease

It has to be considered that MRI and PET may show false-positive signals when the time to surgery is less than 6 months, whereas an epidural disease is the clearest indicator. When in doubt the PI and the steering committee have to decide on the case.

Overall progression-free survival is defined as time from randomization to any (confirmed) tumor progression or death by any cause.

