### Statistical considerations

#### Trial sample size

This study is designed to test if the analgesic efficiency of Kypho-IORT is superior to standard-of-care EBRT in patients with painful vertebral metastases by comparing percentages of patients with a pain reduction of at least 3 points on VAS at defined points in time (day 1, week 2 and 6 after start of treatment).

Assuming a pain reduction of VAS-3 points at day one (first day after Kypho-IORT, one day after the first EBRT) for 40% of the patients after Kypho-IORT vs 5% of the patients after EBRT under standard pain medication (no change of the pretherapeutic pain medication 12 h after Kypho-IORT or 24 h after the first EBRT), the study will require 22 patients in each arm in order to have a two-sided alpha of 0.05 and a power of 0.817. Including a dropout rate of 20% at least 54 patients have to be recruited. The effect size was estimated on the basis of the results of the preceded phase I/II trial [11] and the results of RTOG 9714 [3].

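### Local control is coded as one lesion state per scan, yet the article treats fracture and sintering both as an alternative to relapse and as a sign of progression, so tumour failure and mechanical failure cannot be told apart

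*Protocol article*

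**What the plan says.** Three statements in the protocol article bear on this point.

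- **Secondary endpoints.** Local tumour control is read from the serial CT/MRI scans "by assigning one of the following lesion states: stable, osteoradionecrosis, pathological fracture, sintering progression", or local relapse. This is a choice of one from five. Fractures and sintering progression are also listed as a secondary endpoint of their own.
- **Local tumor control, progression-free survival (assessment).** "At each follow-up visit (after 6 weeks, 3 months and thereafter each 6 months), there will be either a MRI or CT scan". The scan is meant "to determine the response of the treated lesion (stable, osteoradionecrosis, pathological fracture, sintering progression, local relapse"; this second listing does not repeat the restriction to one state.
- **The same section (definition).** "Local control is defined as time span between randomization and local progression". Three CT indicators of local progression follow: growing osteolysis, new epidural disease, and fracture or advancing sintering of the treated vertebra. Suspicion on CT should lead to contrast-enhanced MRI, for which the indicators are a rise in T2 signal and epidural disease. Doubtful cases go to the principal investigator and the steering committee.

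**The concern.** The five states can coexist. A vertebra in which tumour regrows and which collapses fits relapse, pathological fracture and sintering progression at once. The single-choice rule then forces the assessor to drop a finding, and the article gives no order of precedence.

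The two sections also disagree on what collapse means. Under Secondary endpoints it is a different outcome from relapse. In the definition of progression it is one of the signs. A site that follows the first reading records a collapsing, relapsing vertebra as a fracture. A site that follows the second may record a purely mechanical collapse as tumour progression.

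At stake is whether the local-control comparison measures tumour failure, mechanical failure or a mixture. This matters here because only Arm A vertebrae receive cement, and the Discussion credits Kypho-IORT with structural stability. If collapse rates differ between arms, a rule that confuses collapse with relapse need not affect both arms equally.

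**Working it through.** **Is there a figure to reproduce?** Not for this point: the article gives no relapse, fracture or overlap rate for this trial. The only planning figure borrowed below is the group size from Trial sample size, "22 patients in each arm in order to have a two-sided alpha of 0.05 and a power of 0.817". That power belongs to the day-1 pain endpoint (40% vs 5%). It reproduces with a pooled-variance normal approximation: (0.35·√22 − 1.96·√(2·0.225·0.775)) / √(0.4·0.6 + 0.05·0.95) = (1.642 − 1.157)/0.536 = 0.90, giving power 0.817. Nothing here changes it.

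**Step 1: what one code per scan loses.** Let R be the share of lesions with tumour relapse at a scan, F the share with fracture or sintering, and J the share with both.

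- Relapse takes precedence: recorded relapse = R, recorded fracture = F − J.
- Fracture takes precedence: recorded relapse = R − J, recorded fracture = F.
- Either finding counts as local progression (the CT indicators read literally): R + F − J.

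With R = F = 20% assumed:

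| J (assumed) | Relapse first: R / F | Fracture first: R / F | Either counts |
|---|---|---|---|
| 0% | 20% / 20% | 20% / 20% | 40% |
| 5% | 20% / 15% | 15% / 20% | 35% |
| 10% | 20% / 10% | 10% / 20% | 30% |
| 20% | 20% / 0% | 0% / 20% | 20% |

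With separate items both rates stay at 20% in every row. A consistent precedence shortens one category by J and leaves the other intact. Both fall short only if assessors choose differently from case to case; the total loss over the two categories is still J.

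**Step 2: the same in patient counts.** The Background cites mean local control of 77% after EBRT in retrospective series (range 61–89%). So (1 − 0.77) × 22 = 5.1, or about 5 failures in Arm B (range 0.11 × 22 = 2.4 to 0.39 × 22 = 8.6). The earlier phase I/II trial's 12-month local progression-free survival of 93.8% gives 0.062 × 22 = 1.4 failures in Arm A. Treating these as crude counts in 22 patients is a simplification.

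- *Under-count*, if the label alone decided failure and k of the 5 were coded as collapse: k = 0, 1, 3, 5 gives 5/22 (23%), 4/22 (18%), 2/22 (9%), 0/22.
- *Over-count*, if all 5 are kept and m mechanical collapses without tumour growth are added: m = 0, 1, 3 gives 5/22 (23%), 6/22 (27%), 8/22 (36%).

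The values of k and m are assumptions. With about 5 and 1.4 expected events, one or two codes are a material part of the comparison.

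**Step 3: does repeat scanning recover the lost finding?** In part. If regrowth and collapse first appear on different scans, both can be recorded. If they first appear together, one is dropped. After month 3 the scans are six months apart, so both can arise within one interval. A later scan showing both findings poses the same choice again.

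**The case against.** The strongest reply is that the label does not define local control. Local control is time to local progression, and a relapsing vertebra that collapses meets at least one progression indicator whatever state is ticked. Suspicion on CT leads to MRI, whose indicators do not include collapse, and doubtful cases are adjudicated. Coding is also repeated at every visit. The article condenses a full protocol and case report form that are not shown, where separate fields may exist.

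Much of this stands, and it rules out several stronger readings that a reader might infer:

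- *That relapse and fracture are both under-counted.* A consistent choice shortens only one of them.
- *That EBRT relapses disappear.* They need not, because the definition rests on progression rather than on the relapse label.
- *That the fracture endpoint is certainly wrong.* The article ties the five states only to local tumour control and does not say how the separate fracture endpoint is derived.
- *That Arm B is disadvantaged or favoured by a known amount.* The document gives no rate of relapse with collapse in either arm.
- *That a missing improvement state distorts local control.* A shrinking lesion coded as stable is still controlled.

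The reply does not remove the conflict. If collapse counts as progression, the risk moves from under-counting to over-counting. The MRI step helps, but the article does not say that a negative MRI overrides the CT finding, and it warns that MRI and PET may be falsely positive within six months of surgery. Single choice is a rule the article states, not a detail it leaves out.

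**Conclusion.** The point holds in a limited form. The article fixes one state per lesion per scan for states that can coexist, gives no precedence, and contradicts itself on whether fracture or sintering is an alternative to relapse or a sign of progression. When both first appear on one scan, a finding is lost from the code, and the code cannot separate tumour failure from mechanical failure.

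Local failures may be under-counted or over-counted, and the fracture/sintering endpoint may lose events if it is read from the same code. The error per scan equals the share of lesions showing both findings, or the share of mechanical collapses counted as progression. Neither is given, so size and direction remain unknown, and the percentages above are illustrations. An uneven effect between arms is plausible, because only Arm A receives cement, but it is an inference. The day-1 pain endpoint and the sample size are untouched. The change is worth making because it is cheap and, if only single codes are kept, a dropped finding cannot be recovered from them.

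**What to change.** 1. Replace the single state with separate yes/no items for each treated vertebra at each scheduled scan: tumour progression or relapse, pathological fracture, sintering progression, osteoradionecrosis. Define stable as none of these.
2. Derive local control from the tumour item, and the fracture/sintering endpoint from the fracture and sintering items.
3. Reconcile the Secondary endpoints section with the section on local control: state whether fracture or sintering without other evidence of tumour growth counts as local progression, and whether the follow-up MRI decides when it disagrees with CT.

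The cost is a few more case report form fields and a short wording change. No extra scan, visit or patient is needed. If the full case report form already records these findings separately, only the wording and the derivation rule need to change.

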### Patient eligibility

Patients ≥50 years of age with up to 4 treatable vertebral metastases and a localized pain of VAS ≥ 3/10 are eligible to participate.

#### Inclusion criteria

Age ≥ 50 yearsKarnofsky Performance Index ≥60initial pain score (VAS) of at least 3 under standard pain medication (change of the pain medication will me monitored)documented history of cancer (i.e. histological confirmation of the primary tumor)painful osteolytic metastases involving a maximum of 4 vertebrae of the thoracic/lumbar spine, which are accessible for Kypho-IORTwritten informed consent

#### Exclusion criteria

any prior treatment (irradiation, surgery) of the target lesion(s)Lesions cranial to T3 (T1–2 and cervical spine)Tumors infiltrating dorsal vertebral structures (pedicles, lamina) or intraspinal (epidural) extensionpathologic fracture with sintering of > 50%purely osteoblastic/osteosclerotic metastasishigh likelihood for cement leakage (e.g. erosions of the bony borders of the vertebrae), which cannot be controlled otherwise by operating surgeonPregnancy/lactation

### Screening and randomization

After informed consent, all patients will be screened for inclusion and exclusion criteria and obtain a patient ID. A baseline visit will then be performed, which includes the assessment of the KPS and VAS scores, comorbidities and medication, a gross neurological exam, the documentation of the underlying primary cancer and the completion of the QoL questionnaires to obtain baselines. If not performed before, a CT or MRI scan of the spine will have to be performed. After fulfilment of all inclusion criteria and in the absence of exclusion criteria, patients will then be allocated into any of the two arms by block randomization (block sizes of 2 or 4 and stratification by institute). Patients randomized into Arm A will undergo Kypho-IORT, patients randomized into Arm B will undergo standard EBRT (10 × 3 Gy or 1 × 8 Gy).

The intervention (Arm A or B) should begin within a time frame of 14 days after randomization.

### Arm a: Kypho-IORT

Kypho-IORT will be carried out under general anaesthesia as extensively described before [8–11]. All patients will be placed in prone position on a radiolucent table. An intraoperative low-energy x-ray device (Intrabeam®, Carl Zeiss Meditec AG, Oberkochen, Germany) will be used for intraoperative radiotherapy, the centre of the metastasis shall be chosen for the isocenter of the radiation.

The cement augmentation can be performed either as kyphoplasty or in a vertebroplasty technique. Each patient must receive early post-operative imaging of the treated vertebra to assess any leakage of cement. The direction of leakage and the clinical symptoms associated (symptomatic vs. asymptomatic) must be documented at this stage.

### Arm B: external beam radiotherapy

Patients randomized into arm B will receive conventional external beam radiotherapy, either as fractionated radiotherapy with 30 Gy delivered in 10 fractions of 3 Gy or as single-dose irradiation with 8 Gy. Each center must select and adhere to one treatment option (fractionated or singe-dose irradiation). Radiotherapy can be given as per established local standards (3D-conformal radiotherapy or intensity-modulated radiotherapy, local standards for target volume and risk organ delineation, local dose constraints). Patients will need to be seen at least once weekly by physicians and evaluated for adverse reactions.

### Assessment of efficacy parameters

#### Pain

Pain will be assessed at baseline (screening) and then at day 1 (first post-operative day in arm A, first day after treatment begin in arm B), week 2, and week 6 week after treatment and at each follow-up visit there will be an evaluation of pain intensity measured by the visual analogue scale (VAS) together with the current pain medication. Any re-intervention or salvage therapies to the treated site will be also documented.

#### Local tumor control, progression-free survival

At each follow-up visit (after 6 weeks, 3 months and thereafter each 6 months), there will be either a MRI or CT scan of the (complete) spine to determine the response of the treated lesion (stable, osteoradionecrosis, pathological fracture, sintering progression, local relapse) and to monitor for new metastases to other regions of the spine (we recommend the same diagnostic routine, which led to the treatment). Local control is defined as time span between randomization and local progression. Local progression is assessed either by serial CT or MRI scanning. Indicators for local progression in CT scans are:increase in size of osteolytic areasdevelopment of epidural diseaseprogressive sintering/fracture of the treated vertebral body

Once progression is suspected in CT scans, a contrast-enhanced MRI should be performed, whereas indicators of progression areincrease in the T2-signalepidural disease

It has to be considered that MRI and PET may show false-positive signals when the time to surgery is less than 6 months, whereas an epidural disease is the clearest indicator. When in doubt the PI and the steering committee have to decide on the case.

Overall progression-free survival is defined as time from randomization to any (confirmed) tumor progression or death by any cause.

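### Local progression has different CT and MRI indicators, and a patient's follow-up modality is only recommended, so the scanner can affect local control and its use could drift by arm after allocation

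*Protocol article*

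**What the plan says.** All the text at issue is in the protocol article, section on local tumor control and progression-free survival, unless another section is named.

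- Choice of scan at each visit: "there will be either a MRI or CT scan of the (complete) spine". Visits fall at 6 weeks, at 3 months and then every 6 months.
- Constancy of modality: "we recommend the same diagnostic routine, which led to the treatment". This is advice, not a requirement.
- Endpoint: "Local progression is assessed either by serial CT or MRI scanning".
- CT signs: "Indicators for local progression in CT scans are:increase in size of osteolytic areasdevelopment of epidural diseaseprogressive sintering/fracture of the treated vertebral body".
- MRI signs, and the step from CT to MRI: "Once progression is suspected in CT scans, a contrast-enhanced MRI should be performed, whereas indicators of progression areincrease in the T2-signalepidural disease".
- Caveat: "MRI and PET may show false-positive signals when the time to surgery is less than 6 months". Epidural disease is named as the clearest sign.
- Doubtful cases: "When in doubt the PI and the steering committee have to decide on the case".

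Under Screening and randomization, baseline imaging may be CT or MRI, and randomisation is in blocks of 2 or 4 stratified by institute. Local tumor control is listed under Secondary endpoints.

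**The concern.** Two partly different sets of signs feed one endpoint, and which set applies depends on the scanner used at that visit. If the mix of scanners were fixed before randomisation, this would mainly add noise and make the result harder to interpret. The article does not fix it. One arm is surgery under general anaesthesia and the other is external beam treatment, so staff will know the allocation when they order the follow-up scan. A choice made at that point is not protected by randomisation. If CT and MRI were used in different proportions in the two arms, local control could differ between arms with no true difference. A change of scanner within a patient also leaves no like-for-like earlier image against which to judge an increase.

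The article supplies a possible reason for such drift. Its false-positive warning for MRI concerns the first 6 months from surgery. Protocol surgery occurs only in Arm A, and the 6-week and 3-month scans both fall in that window. An investigator could reasonably prefer CT early in Arm A and have no matching reason in Arm B.

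**Working it through.** The plan gives no figure for this endpoint definition, so the main check sets the two lists side by side.

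| Sign at the treated vertebra | On CT list | On MRI list | Consequence in the text |
|---|---|---|---|
| Epidural disease | yes | yes | Same under either scanner |
| Osteolytic growth | yes | no | CT follow-up: suspicion, and MRI should follow. MRI follow-up: not a listed sign |
| Advancing sintering or fracture | yes | no | Recorded as a lesion state under either scanner, but a listed sign of progression only for CT |
| T2 rise | no | yes | MRI follow-up: a listed sign. CT follow-up: no CT sign, so no MRI is triggered |

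Three situations follow.

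1. T2 rise, no CT sign. The work-up step starts only from suspicion on CT, so it cannot reach this case. The scanner decides whether the question is raised.
2. Osteolytic growth in a patient followed by MRI. The MRI list does not name it, and no step leads from MRI to CT.
3. Positive CT, then an MRI with neither T2 rise nor epidural disease. No rule says which result stands. Committee review applies only if someone is in doubt.

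**Illustration of size.** Every input here is an assumption; the documents give none of them. Suppose there is no true arm difference, epidural disease occurs in 5%, CT-only signs in c = 5% to 15%, and T2-only rise in m = 3% to 10%, all independent and all counted as events.

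- Rate under CT = 1 − 0.95 × (1 − c): from 1 − 0.95 × 0.95 = 9.75% to 1 − 0.95 × 0.85 = 19.25%.
- Rate under MRI = 1 − 0.95 × (1 − m): from 1 − 0.95 × 0.97 = 7.85% to 1 − 0.95 × 0.90 = 14.5%.
- Spurious difference (A − B) = (CT share in A − CT share in B) × (CT rate − MRI rate).
- CT − MRI ranges from 9.75 − 14.5 = −4.75 points to 19.25 − 7.85 = +11.4 points.
- CT shares 80% v 30%: 0.5 × (−4.75) = −2.4 to 0.5 × 11.4 = +5.7 points.
- CT shares 60% v 40%: 0.2 × (−4.75) = −1.0 to 0.2 × 11.4 = +2.3 points.

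With 54 patients, about 27 per arm, +5.7 points is 27 × 0.057 = 1.5 patients and +2.3 points is 27 × 0.023 = 0.6 of a patient. For scale, the Background reports 93.8% local progression-free survival at 12 months in the phase I/II trial, a complement of 6.2%.

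**What is not affected.** The sample size rests on day-1 pain response. The normal approximation with pooled variance for 40% v 5% and 22 per arm gives power 0.8167, against the stated 0.817. Imaging does not enter it.

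**The case against.** A reader might infer that each listed sign is automatically an event, so that a vertebra is progressed or controlled purely by scanner. The article does not support that. The signs are called indicators, the MRI list sits inside the sentence on work-up after a suspicious CT, the text warns against early false positives, and doubtful cases go to the PI and steering committee. An isolated early T2 rise is the kind of case these provisions address. This stands. It lowers the discordance, and the illustration above, which omits these safeguards, overstates it. It does not reach situations 1 and 2, where no doubt need arise, and it gives no rule for situation 3.

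Sintering and fracture can be recorded as lesion states on either scanner, and sintering progression is also a separate secondary endpoint. This stands too, so osteolytic growth is the main CT-only sign.

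Drift between arms is not shown. Randomisation is stratified by institute, which tends to balance centre habits, and the recommended modality is set before allocation. Nothing suggests a mix as unequal as 80% v 30%. All true, but stratification does not constrain what is ordered for a given patient after allocation, and a recommendation does not bind. That treatment is open and that modality may change are inferences: the article describes no masking and forbids no change.

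A condensed article may leave reading rules to the full protocol, and handling of modality in the analysis to the SAP. For that reason the point rests only on what the article states: two different lists and a modality that is merely recommended.

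**Conclusion.** The point holds in a limited form. Classification of local progression can depend on the scanner, and the choice of scanner is open after allocation in arms that cannot realistically be masked. Local control is affected, and possibly overall progression-free survival, which counts confirmed progression of any kind.

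The size and direction are unknown. A reader might take −2.4 to +5.7 points as an estimate of bias, or infer that one arm is favoured. Neither follows: all rates and CT shares are assumed, the range includes zero, and the upper end pairs the most extreme values. It shows only that a shift of a patient or so per arm is conceivable on an endpoint with few expected failures.

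The primary endpoint and sample size are unaffected. The change is worth making because it is cheap and closes a route to bias that the article's own MRI caveat makes plausible.

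**What to change.** In the section on local tumor control:

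1. Replace the recommendation with a requirement. Each patient's follow-up modality is recorded before randomisation and used at every scheduled visit. Extra scans remain allowed for suspected progression. If the modality becomes infeasible, the other may be used and the change is recorded as a deviation.
2. State one definition of local progression that applies to both modalities, including which result stands when CT is positive and MRI negative. Which signs belong in it is for the sponsor to settle.
3. Report time to new epidural disease, the one sign on both lists, as a sensitivity analysis.
4. Report modality use by arm and visit descriptively. Do not stratify the main analysis by modality: with 54 patients the events will be few and strata would cost precision.

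Cost: a short protocol edit and one baseline CRF field, with no additional scheduled scans. The downside is that centres lose the freedom to switch scanner. The epidural-disease analysis will rest on even fewer events than the main one and can only support it.
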